## 7. ETHICAL CONSIDERATIONS

This project is lawful as it is to be conducted under stringent guidelines as set by The University of Sydney Ethic Office Committees. All research conducted will be done so with the approval and consent from all participants.

The research will be conducted in an environment well known to all participants to make them most comfortable. The researcher will ensure to maintain the highest research standards as imposed by the NHMRC. In ensuring to maintain high standards of wellbeing for each participant, open communication lines between the researcher and the participants will be maintained. At no time will participants be pressured to participate in the investigation and may withdraw at any time.

The participants will always have access to the contact details of the researcher and most importantly after the investigation. All participants will be made aware that any questions they have will be answered without judgement and reasonable action will be taken to ensure that they are comfortable with the research taken. If at any time they require further assistance that the researchers cannot provide, the university has a knowledgeable course coordinator whom they and the researchers can work with to provide the necessary assistance the participant requires.

The importance of this research is to develop technology-based physical education courses for university settings so that the results of this study are useful for universities to assist teachers in maintaining and improving physical education courses accompanied by affordable technology for students.

The researchers will endeavour to understand any cultural sensitivities through consultation with the curriculum development team, course coordinator and the Dean of Faculty of Sport and Health Education and from [name]'s experiences as academic staff member. Furthermore, the researcher will continue to develop their understanding of culturally sensitive matters through focus group discussion.

As the researcher is a citizen of Indonesia and is current staff member of Universitas Pendidikan Indonesia. He is aware of a large proportion of the issues which exist in a university setting, particularly as a Lecturer of physical education at Universitas Pendidikan Indonesia. Also, he is well aware of the cultural norms, but also the local cultural norms as an academic staff member of Universitas Pendidikan Indonesia.

The USyd student researcher is a current academic staff member at Universitas Pendidikan Indonesia (UPI), however, during the data collection process he will be on study leave from UPI. Therefore, he will not be coordinating or teaching the unit during this time. He also does not have any information regarding which students will enrol the unit. He may however know the teaching staff who will volunteer to participate in this study, however, it will be made clear to them that they can withdraw from the study at any time.

## 8. SAFETY CONSIDERATIONS

The COVID-19 pandemic situation could impact the proposed study. The first implication regards overseas travel, as this study will be conducted in Indonesia. Hence, safety travel protocols will be followed. This study will also involve class interventions and observations which in the current situation could be conducted in the online environment.

## 9. OUTCOMES

### 9.1 Primary outcome

Difference in physical activity levels, knowledge and motivation at 16 weeks' time point compared to physical activity levels measures at baseline.

Three outcomes were measured in the pre-and post-intervention. First, The International Physical Activity Questionnaire-Short Form (IPAQ) was used to measure the student's physical activity levels. IPAQ is internationally recognised as a valid and reliable questionnaire for measuring physical activity levels. The IPAQ is publicly available, it is open access, and no permissions are required to use it. The IPAQ is suitable for adults between 15 and 69 years of age and is primarily used for population surveillance of physical activity levels. The IPAQ short form records the activity of four intensity levels: 1) vigorous-intensity activity such as aerobics, 2) moderate-intensity activity such as leisure cycling, 3) walking, and 4) sitting. Then, to measure student's motivation, the Behavioural Regulation Exercise Questionnaire (BREQ-2) was used which has 19 questions using a 5-point Likert scale for responses. BREQ-2 is a valid and reliable measure five subscales of physical activity motivation: Amotivation, External Regulation, Introjected Regulation, Identified Regulation, and Intrinsic Regulation within university students population. Lastly, to measure physical activity knowledge, we developed physical activity knowledge quizzes consisting of 20 multiple choices question based-on the learning outcome of the physical education course. To demonstrate construct validity, two physical education experts reviewed the quizzes whether the questions were

aligned with the learning outcomes. Then, test-retest reliability was performed to measure the consistency of the quizzes with 20 university students within two weeks. The coefficient correlation between test and retest was high  $r=0.833$  ( $P < 0.05$ ).

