## 6. RESEARCH PLAN / STUDY DESIGN

### 6.1 Type of study

This is a two-arm parallel, randomised controlled trial of a technology-supported physical education course intervention for students enrolled in an elective unit of study. The six lecturers who agree to participate will be randomly assigned to the intervention or control group. Students who enrol randomly by the University system with the participated lecturers of physical education course will be invited to participate in the study. The intervention lecturers will have lecturer training and implement the 16-week technology-supported physical education course intervention for one semester. The Primary outcome is to examine the difference in students' physical activity levels, knowledge and motivation at post-test (at the completion of a 16-week semester) compared with the control group. The secondary outcome is students' experience and enjoyment of the technology-supported physical education course intervention.

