### 6.2 Sample size including power calculation

The sample size calculation is based on the difference in change in the primary outcome (physical activity) from pre- to post-intervention in both group (intervention and control group). Based on previous studies on technology-based physical activity interventions in university students, mean effect sizes of around  $d = 0.5$  are expected in analyses. To detect such intervention effects in two-sided significance testing ( $\alpha = .05$ ) with a power of 80%, a sample size of 128 participants is required. Taking into account an expected study drop-out of about 20%, 150 participants must be included in the study and participants response rate of about 50%, hence, 300 students (six classes of physical education course) will be invited.

Number of Participants

N=6 physical education course lecturers

(a) n=3 will be assigned to the intervention group,

(b) n=3 will be assigned to the control group.

n=300 students will be randomised 1:1 to either an intervention arm

(a) n=150 a technology-supported physical education course (intervention group)

(b) n=150 non-technology-supported physical education course (control group).

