### 6.3 Statistical analyses

All variables will be checked for normality using the Shapiro-Wilk test. Independent samples t-tests or Mann–Whitney U-tests will then be conducted, as appropriate, to examine: (1) pre-test differences between groups and (2) pre-test differences between students who completed the study and those lost to follow-up. If variables significantly differ between groups, they will be appropriately adjusted in the main analyses. Descriptive statistics will be presented (mean and standard deviation) for each group separately.

Linear mixed models will be used to analyse the differential change between groups on all outcomes from pre-test to post-test, using pre-test data as the covariate. Linear mixed models will be used because these models are robust enough to withstand the biases from missing data. All analyses will be conducted using SPSS 28.0 (Chicago, IL, USA). The level of significance will be set at  $p < 0.05$ .

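### Section 6.2 powers the trial on physical activity alone, other sections name three primary outcomes with no success rule, and section 9.1 gives the wrong comparator

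*Protocol*

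**What the plan says.** **How many primary outcomes.** Section 6.2 uses the singular and names it: "The sample size calculation is based on the difference in change in the primary outcome (physical activity) from pre- to post-intervention". Section 6.1 lists three: "The Primary outcome is to examine the difference in students' physical activity levels, knowledge and motivation at post-test". The outcomes row of the synopsis and section 9.1 list the same three, and the hypothesis in the synopsis and in section 4 covers all three. Section 9.2 lists only the students' experience of the app as secondary (the synopsis and 6.1 add enjoyment). Knowledge and motivation therefore cannot be read as secondary anywhere in the protocol.

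**How they are tested.** Section 6.3 fits linear mixed models to all outcomes, comparing the change between groups with the pre-test value as covariate, at p < 0.05. It gives no order of testing, no split of alpha and no statement of which results make the trial a success.

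**Against what they are compared.** The synopsis and 6.1 compare with the control group at the end of the 16-week semester. Sections 6.2 and 6.3 use the between-group difference in change. Section 9.1 says instead: "Difference in physical activity levels, knowledge and motivation at 16 weeks' time point compared to physical activity levels measures at baseline".

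**How motivation is scored.** Section 9.1 measures it with the BREQ-2, described as having "five subscales of physical activity motivation: Amotivation, External Regulation, Introjected Regulation, Identified Regulation, and Intrinsic Regulation". It names no single motivation score.

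**The concern.** The sample size fits one definition of the primary outcome, while the synopsis, 6.1 and 9.1 use another. A later document cannot follow both. Until this is settled, a positive trial has at least three possible meanings: physical activity differs, any of the three outcomes differs, or all three differ. These have different false-positive rates and different power, and 6.2 describes only the first. The choice could then be made after the results are known.

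The 9.1 wording adds a second conflict. Read literally, it sets knowledge and motivation scores against baseline physical activity, which has no meaning. Read generously, it is a change from baseline within a group. Both arms receive the same 16-week content (Table 1 in section 6.6), and the knowledge quiz is built on the course's learning outcomes. Such a contrast could be positive in both arms even if the app added nothing.

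**Working it through.** **Inputs.** From 6.2: d = 0.5, two-sided alpha 0.05, power 80%, stated N = 128, allocation 1:1. From 6.1 and 9.1: three primary outcomes. From 6.3: each tested at 0.05. Not given in the protocol: the correlations between the outcomes, and the expected effects on knowledge and motivation.

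**Step 1: reproduce the plan's figure.** Normal approximation, per arm: n = 2(1.960 + 0.842)² / 0.5² = 62.8, so 63 per arm and 126 in total. The exact two-sample t-test gives 63.8, so 64 per arm and 128 in total, with power 80.1%. The stated 128 is therefore a calculation for one endpoint at 0.05, with nothing reserved for further outcomes.

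**Step 2: if success on any one of three is enough.** For independent tests the family-wise error is 1 − (1 − 0.05)³ = 1 − 0.857 = 0.143. Simulating three equally correlated two-sided tests gives:

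| Assumed correlation | Family-wise error |
|---|---|
| 0 | 14.3% |
| 0.3 | 13.6% |
| 0.5 | 12.5% |
| 0.7 | 10.9% |

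**Step 3: if all three must succeed.** Alpha needs no adjustment, but power changes. If each outcome has 80% power (d = 0.5 for each) and they are independent, joint power is 0.8³ = 0.512. Positive correlation raises it, to at most 80% when the three are perfectly correlated. The d = 0.5 in 6.2 was chosen for physical activity; applying it to knowledge and motivation is an assumption.

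**Step 4: if three are kept with a Bonferroni split.** Alpha per test is 0.05 / 3 = 0.0167. With 64 per arm, power for each outcome is 65.6%. Restoring 80% per outcome needs 86 per arm, or 172 in total before drop-out, and 172 / (1 − 0.20) = 215 after it.

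**Step 5: if physical activity is the only primary outcome.** Alpha stays at 0.05, and 128 stays as computed in step 1.

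**Step 6: the comparator, section by section.**

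| Place | Comparison |
|---|---|
| Synopsis, outcomes | Control group |
| 6.1 | Control group |
| 6.2 | Difference in change between groups |
| 6.3 | Difference in change between groups, adjusted for pre-test |
| 9.1 | Baseline physical activity |

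Section 9.1 stands alone against the other four.

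These figures accept 6.2's calculation as it stands, without any allowance for clustering by lecturer.

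**The case against.** **A statistical analysis plan may set the multiplicity rule and the BREQ-2 scoring.** This is fair as far as it goes. A missing testing order, composite score or scoring direction is not an error in this protocol. But which outcome is primary, and against what it is compared, are stated here in conflicting ways, and a later plan would have to contradict one section or another.

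**Section 9.1 might seem to show that the randomised comparison is abandoned.** A reader could infer this from that sentence alone. The protocol does not support it: 6.3 specifies a between-group model adjusted for the pre-test value, and the synopsis, 6.1, 6.2 and the hypothesis are all comparative. What remains is one wrong sentence, though it stands in the section that defines the primary outcome.

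**There might seem to be seven primary tests.** One could count one IPAQ score, one quiz score and five BREQ-2 subscales, and get 1 − 0.95⁷ = 30%. The protocol does not say that the subscales will be tested separately as primary outcomes, and 9.1 speaks of three outcomes. A single motivation index would keep the count at three. The 30% is therefore not a property of the plan as written.

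**The two magnitudes cannot both apply.** This is correct. The hypothesis joins the three outcomes with *and*, which may mean that all must succeed; then the 14% does not arise. If any one is enough, the 51% does not arise. Both are also independence figures, whereas section 3 of the protocol argues that knowledge and motivation are associated with physical activity. The ranges above reflect that. The objection limits the size of the problem but does not remove it, because the protocol never says which reading holds.

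**Conclusion.** The point stands on two contradictions within the protocol. First, 6.2 powers one primary outcome while the synopsis, 6.1 and 9.1 declare three, and 6.3 tests all at 0.05 without a success rule. The consequence depends on the reading:

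- **Any one is enough:** family-wise error of about 14% if independent, or about 11% to 14% at assumed equal correlations of 0.7 to 0.3.
- **All are needed:** joint power of about 51% if independent with d = 0.5 for each outcome, and never above the 80% stated for one.

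Second, the comparator in 9.1 contradicts four other places. This is a faulty definition, and the planned analysis itself remains between-group. The first contradiction is the weightier, because it decides what counts as a positive trial. Separate testing of the BREQ-2 subscales would add tests, but nothing in the protocol commits to it.

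**What to change.** Make IPAQ physical activity the single primary outcome, as 6.2 already assumes, analysed by the pre-test-adjusted between-arm comparison in 6.3 at two-sided 0.05. Make knowledge and motivation secondary. Amend the hypothesis (synopsis and section 4), the synopsis outcomes, 6.1, 9.1 and 9.2 to match, and reword 9.1 so that the comparison is with the control arm at week 16.

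This changes wording only, and on this point leaves N = 128 and alpha 0.05 as they are. The downside is that knowledge and motivation lose primary status, which narrows the primary hypothesis.

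If the sponsor prefers to keep three primary outcomes, that is a legitimate choice. The protocol should then state whether one or all must succeed and restate the power to match. With Bonferroni, for example, power is about 66% per outcome at N = 128, and 172 students before drop-out would be needed for 80% per outcome. The 9.1 comparator needs correcting in either case.

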## 9.2 Secondary outcome(s)

- Student's experience using technology-supported physical education app

## 10. DATA MANAGEMENT

- *Source Data*  
Measurement will be conducted via online questionnaire using RedCap. Audio recording for FGD.
- *Data Capture Methods*  
Audio recordings of focus group discussions will take place to ensure that the conversations and responses are captured correctly and can be transcribed verbatim at a later time. The online survey will be hosted in University of Sydney via RedCap. REDCap is a secure web platform for building and managing online databases and surveys
- *Data Storage*  
Electronic files of consent forms, audio recordings, and interview transcripts will be stored on the University-licensed eNotebook (LabArchives) platform during the project. The eNotebook is an electronic notebook that stores data on secure servers within NSW. The eNotebook is named Tech-supported PE for PA at university Project and will be owned by the student researcher, [name] (UniKey: [name])
- *Record Retention*  
The 5 year period complies with relevant legislation from the State Records Authority of NSW. The study is recruiting participants who are adults (aged older than 18 years).
- *Archiving*
- Study materials will be stored on the University-licensed eNotebook (LabArchives) platform during the project. The eNotebook is an electronic notebook that stores data on secure servers within NSW. The eNotebook is named Tech-supported PE for PA at university Project and will be owned by the student researcher, [name] (UniKey: [name])

## 11. TIMELINES / MILESTONES

Predictive timeline for this study:

- Lecturer's recruitment first half of August 2022
- Lecturers training second half of August 2022
- Student's recruitment September 2022
- Pre-test September 2022
- Intervention September 2022 to January 2023
- Post-test January 2023
- Data Analysis January to February 2023
- Publication March 2023

## 12. FINANCIAL

Usyd student's researcher is supported by the Indonesia Endowment Fund for Education Scholarship (LPDP RI) under a doctoral degree scholarship.

### 13. PUBLICATION POLICY / DISSEMINATION OF RESULTS

Overall result of this project will be disseminated in journal publications and a PhD thesis.

